### Objectives {7}

Primary objective: To determine if tapering of medically prescribed opioids in a long-term non-cancer pain population is superior to control in reducing dispensed opioids and non-inferior regarding participants’ report on pain, pain cognitions, physical and mental health, quality of life, and functioning.

Secondary objective: To determine if a reduction in opioid intake displays stability over time.

Research hypothesis: Tapering of opioids in a structured intervention will reduce opioid intake by at least 50% and is superior to controls in reducing dispensed opioids.

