### Trial design {8}

The design of the present study is an RCT, which is under recruitment and conducted among patients with long-term pain who have been accepted to undergo a structured intervention aiming to taper opioid long-term treatments. The study population will be randomly allocated to either (1) the start of tapering opioids immediately or (2) the control group who will return to usual care and commence tapering of opioids 4 months later. A 12-month follow-up after the start of the intervention is included (Fig. 1). The study lies within a superiority framework. Primary endpoints are hypothesized to generate a decrease in opioid use in comparison to controls.

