#### Primary outcomes

Consumption of opioids, measured as MME, will be evaluated using data extracted from the Swedish drug register of the National Board of Health and Welfare (SDPR) where registration of all withdrawals of prescribed drugs is made. MME will be calculated using these data. At all baseline visits and 12-month follow-ups, the MME will be calculated for the preceding 90 days, but at 4 months after the intervention, the dose will be calculated for the preceding 30 days as the intervention is estimated to last approximately 3 months.

Self-reported opioid consumption will also be evaluated and reported in MME. Calculation of morphine equivalent dose will be performed with conversion factors used in Cochrane review [7].

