#### Secondary outcomes

Secondary outcomes are effects on pain, pain cognitions, mental health, life quality, and physical and psychological functioning using validated questionnaires registered in SQRP [32]. Pain rating will be evaluated using NPRS. Pain cognitions are mapped with the Tampa Scale of Kinesiophobia (TSK), Pain Catastrophizing Scale (PCS), and Chronic Pain Acceptance Questionnaire (CPAQ-8). Hospital Anxiety and Depression is applied to assess mental health, and RAND-36 will be used to assess the quality of life and functioning entailing physical, mental, and general health.

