## Statistical methods

### Statistical methods for primary and secondary outcomes {20a}

All statistical analyses will be performed with the SPSS software (version 25, IBM Inc). Continuous data will be expressed by means, standard deviation and 95% confidence interval, and categorical data in numbers and percentages.

The intervention arm (tapering opioids) will be compared with control (waiting list) for primary and secondary outcomes at 4 months of follow-up. Statistical analysis of differences between groups will be performed per protocol (attending follow-up 4 months after the start of the intervention and attending second baseline visit in controls) with a paired *t*-test regarding the primary outcome and a Wilcoxon signed-rank test regarding secondary outcomes.

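### The primary objective includes non-inferiority on patient-reported outcomes, which conflicts with the declared superiority framework, the outcomes' secondary status and the paired difference test specified for them

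*Protocol article*

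**What the plan says.** - **Objectives {7}.** One sentence sets a joint primary objective: tapering "is superior to control in reducing dispensed opioids and non-inferior regarding" a list of patient-reported domains covering pain, pain cognitions, health, quality of life and functioning. The research hypothesis in the same section concerns opioids only: the intervention "will reduce opioid intake by at least 50% and is superior to controls in reducing dispensed opioids".
- **Trial design {8}.** "The study lies within a superiority framework", followed by "Primary endpoints are hypothesized to generate a decrease in opioid use in comparison to controls". Non-inferiority is not mentioned.
- **Outcomes {12}.** The domains named in the primary objective are listed again, now as secondary: "Secondary outcomes are effects on pain, pain cognitions, mental health, life quality, and physical and psychological functioning".
- **Statistical methods {20a}.** Differences between groups are analysed per protocol, meaning those who attend the 4-month follow-up or, in controls, the second baseline visit. The tests are a paired *t*-test for the primary outcome and "a Wilcoxon signed-rank test regarding secondary outcomes".
- **Sample size {14}.** The calculation uses one standardised effect of 0.5, 80% power, alpha 0.05 and 10% dropout, giving 70 per group. It follows the definition of an opioid responder and does not mention non-inferiority.
- **Primary outcomes, under Outcomes {12}.** After register-based MME the text adds: "Self-reported opioid consumption will also be evaluated and reported in MME".

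**The concern.** Superiority and non-inferiority need different hypotheses and different decision rules. Half of the primary objective is a non-inferiority claim, yet no later section carries it forward. The framework is superiority, the outcomes are secondary, and the named procedure tests for a difference.

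The signed-rank test adds a second problem. It works on pairs, and participants in two randomised arms are not paired. Applied within an arm it describes change from baseline, which is not a comparison with control.

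At stake is what the trial may say about pain and function. The Background reports that patients fear more pain on tapering and that a systematic review found no evidence on the efficacy or safety of tapering methods. A statement that opioids fell and patients were no worse would therefore carry weight. Under the plan as written, the easiest route to that statement is a non-significant test, or a margin chosen once the data are known.

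**Working it through.** **1. Statements side by side**

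| Section | Patient-reported outcomes are treated as |
|---|---|
| Objectives {7}, primary objective | part of the primary objective, non-inferiority |
| Objectives {7}, research hypothesis | not mentioned |
| Trial design {8} | not mentioned; superiority framework |
| Outcomes {12} | secondary |
| Sample size {14} | not mentioned |
| Statistical methods {20a} | paired test of difference, per protocol, no criterion for non-inferiority |

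The first row cannot be reconciled with the others.

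**2. The plan's own sample size**

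Inputs from Sample size {14}: d = 0.5, power 80%, alpha 0.05 (taken as two-sided), dropout 10%.

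n per arm = 2 × (1.960 + 0.842)² / 0.5² = 62.8, so 63. Allowing for dropout, 63 / 0.9 = 70.

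This matches the stated figure exactly, as a superiority comparison of two independent means. A paired *t*-test would give 34, or 38 after dropout, which does not match. The arithmetic is sound, and it was done for a two-arm superiority question.

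**3. What a non-significant result would mean**

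Assumptions: 63 evaluable per arm, unadjusted two-sample comparison, normal approximation, two-sided 5%.

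Power = Φ(δ × √(63/2) − 1.960), with δ the true worsening in SD units and √31.5 = 5.612.

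- δ = 0.3: Φ(1.684 − 1.960) = Φ(−0.276) = 0.391, so non-significant about 61% of the time.
- δ = 0.2: Φ(1.122 − 1.960) = Φ(−0.838) = 0.201, so non-significant about 80% of the time.

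**4. What a proper non-inferiority test could show**

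The article gives no margin, so the margins *m* below are assumptions. Each row is for one outcome, with one-sided 2.5% and a true difference of 0.

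Power with 63 per arm = Φ(m × 5.612 − 1.960). For 80% power, n per arm = 2 × (1.960 + 0.842)² / m², then divided by 0.9 for dropout.

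| Assumed margin (SD) | Power, 63 per arm | n per arm for 80% | with 10% dropout |
|---|---|---|---|
| 0.5 | 80% | 63 | 70 |
| 0.4 | 61% | 99 | 110 |
| 0.3 | 39% | 175 | 195 |
| 0.2 | 20% | 393 | 437 |

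**5. Sensitivity to baseline adjustment**

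If baseline and follow-up scores correlate at ρ (assumed 0.5 to 0.7), adjustment multiplies the standardised effect by 1/√(1 − ρ²), that is 1.155 to 1.400.

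- Margin 0.3 SD: power rises from 39% to 49–65%.
- Margin 0.5 SD: power rises from 80% to 90–98%.
- The 61% in step 3 falls to 51–35%.

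Adjustment helps materially, but a tight margin stays underpowered over this range.

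**The case against.** **A margin may be in a separate analysis plan.** This is fair, and the missing margin alone would not be a finding. But an analysis plan can only add a margin. It cannot make a non-inferiority objective agree with a superiority framework, a secondary classification and a named paired test that the article itself states.

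**The plan also reports 95% confidence intervals.** A reader might infer that 'non-inferior' can only mean a non-significant p-value. That goes too far. Statistical methods {20a} expresses continuous data with 95% confidence intervals, and a signed-rank procedure can be shifted by a margin. However, the text does not say that the intervals are for between-arm differences, and it sets no rule for reading them.

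**The figures do not model the stated test.** Correct. They assume a two-sample comparison because the paired test has no between-arm power to compute. They illustrate scale, and step 5 shows how adjustment moves them.

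**The aims are framed neutrally elsewhere.** The abstract speaks of assessing effects, and the hypotheses concern opioids only. This stands, and it points to the simplest cure: bring the primary objective into line with the rest.

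**Two tempting extensions are not supported.**
- A reader might infer two co-primary outcomes with inflated type I error, because self-reported MME appears under the primary headings. But the objective speaks of dispensed opioids, Data management {19} derives primary outcomes from the register and files self-report under additional data, and {20a} refers to a single primary outcome. This is loose placement.
- A reader might infer that every questionnaire must pass non-inferiority jointly. No section sets that rule.

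**Conclusion.** The concern holds as an internal contradiction. Non-inferiority sits in the primary objective and is contradicted or left unsupported by Trial design {8}, Outcomes {12} and Statistical methods {20a}. As specified, the plan cannot yield a between-arm non-inferiority conclusion on any patient-reported outcome.

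On size: reading non-significance as 'no worse' would miss a true worsening of 0.3 SD about 61% of the time without adjustment. The planned numbers give 80% non-inferiority power on a single outcome only at a margin of about 0.5 SD. These figures rest on 63 evaluable per arm, a two-sample normal approximation and assumed margins; baseline adjustment would improve them.

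A reader might infer that the sample size is wrong or that the trial is too small. The documents do not support that: 70 per group reproduces exactly, and it would serve a 0.5 SD margin on one outcome. This point also leaves the superiority question on register MME untouched.

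**What to change.** Choose one of two routes.

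1. **Drop the claim.** Delete the non-inferiority wording from Objectives {7}. Report the patient-reported outcomes as secondary, as between-arm differences with 95% confidence intervals, and make no 'no worse' statement.
2. **Keep it, narrowed.** Make non-inferiority a key secondary objective on a named outcome. Fix the margin in scale points before any outcome data are compared. Judge it by a baseline-adjusted between-arm 95% confidence interval in both the all-randomised and per-protocol sets, and state the power at that margin. Which outcome to name, and whether to test it only after the primary succeeds, are the sponsor's choices; the documents do not rank one scale above another.

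Under either route, replace the signed-rank test with a between-arm analysis. As a minor wording point, say plainly that register MME is the primary outcome and self-reported MME is supportive.

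The cost is a protocol amendment and a matching registry update, which section {25} already provides for; no new data are needed. What is given up is a broad non-inferiority claim across all the questionnaires.

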### Sample size {14}

A “responder” to treatment is a participant who experiences at least a 50% reduction in opioid consumption [28]. Estimation of sample size was based on an effect size of 0.5 (Cohen’s *d*) 80% power, *α* = 0.05, and drop-off at 10%. The results from the calculation indicated the need for 70 individuals in each group.

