## Assignment of interventions: allocation

### Sequence generation {16a}

The allocation sequence is generated by computer to intervention or control in ratio 1:1 and is thereafter kept in sealed envelopes prepared by independent staff for an allocated group of 140 participants. Sealed envelopes will be kept in Lund and allocation will consequently take place in Lund.

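### The at-least-50% part of the hypothesis, and the responder definition that goes with it, enter neither the sample size nor any stated analysis

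*Protocol article*

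**What the plan says.** The research hypothesis in Objectives {7} has two parts: "Tapering of opioids in a structured intervention will reduce opioid intake by at least 50% and is superior to controls in reducing dispensed opioids". The primary objective in the same section carries only the second part for opioid use, namely that tapering "is superior to control in reducing dispensed opioids". Trial design {8} agrees: "Primary endpoints are hypothesized to generate a decrease in opioid use in comparison to controls".

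Sample size {14} opens by defining a responder, who "is a participant who experiences at least a 50% reduction in opioid consumption". The next sentence turns to another quantity: "Estimation of sample size was based on an effect size of 0.5", expressed as Cohen's d, with 80% power, alpha 0.05 and 10% drop-off.

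Outcomes {12} makes the primary outcome a continuous one, MME from the drug register. It is averaged over 90 days at baseline visits and at 12 months, and over 30 days at 4 months. Statistical methods {20a} compares the arms at 4 months with a t-test on that outcome. The only percent-change analysis is in {20b}. It runs within each group from the end of tapering (4 or 8 months) to 12 months.

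**The concern.** The 50% threshold is stated twice, once as a hypothesis and once as a definition at the head of the sample-size section. After that it disappears. No outcome counts responders, no test or confidence limit is set against 50%, and the one percent-change analysis measures whether the tapered dose is kept, not how far intake fell from baseline.

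The trial could therefore reach significance on MME and leave half of its hypothesis unanswered, with no rule on what would support the 50% statement. Placing the responder definition directly before the sizing inputs also invites the reader to think that 140 participants were chosen to compare responder rates. They were not.

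**Working it through.** **1. Reproduce the stated size.** Inputs from Sample size {14}: d = 0.5, power 80%, alpha 0.05 (taken as two-sided), drop-off 10%. From Sequence generation {16a}: "The allocation sequence is generated by computer to intervention or control in ratio 1:1".

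n per arm = 2 × (1.960 + 0.842)² / 0.5² = 62.8, so 63. With drop-off: 63 / 0.9 = 70.

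This matches the stated "need for 70 individuals in each group". One-sided testing would give 50, then 56. A paired design at d = 0.5 would give 34 pairs, then 38. The size is that of a two-sided comparison of two independent means. No proportion and no 50% threshold enters it.

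**2. What a significant result would show.** With 63 per arm (124 degrees of freedom), the smallest significant observed difference is 1.979 × √(2/63) = 0.353 SD. To express this as a share of the mean, multiply by the coefficient of variation (CV = SD/mean). The article gives neither SD nor mean, so the CVs are assumed:

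| Assumed CV of MME | Smallest significant difference, % of mean | d = 0.5, % of mean |
|---|---|---|
| 0.7 | 0.353 × 0.7 = 25% | 35% |
| 1.0 | 35% | 50% |
| 1.5 | 53% | 75% |

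These are between-arm differences. They approximate the tapering arm's own reduction only if the waiting-list arm stays near its baseline.

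**3. Power of a responder comparison at the present size.** Take n = 63 per arm, two-sided 0.05, with p₁ and p₂ the two responder rates and p̄ their average:

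power = Φ{ [ (p₂ − p₁) − 1.960 √(2p̄(1−p̄)/n) ] / √[ (p₁(1−p₁) + p₂(1−p₂))/n ] }

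For 30% vs 50%: (0.20 − 1.960 × 0.0873) / 0.0854 = 0.34, so power is 63%. All rates below are assumed, since the article gives none:

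| Control vs tapering | Power |
|---|---|
| 30% vs 50% | 63% |
| 20% vs 40% | 69% |
| 10% vs 30% | 81% (83% by the arcsine formula) |
| 20% vs 50% | 95% |

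If the true effect is no more than a normal shift of 0.5 SD that is then cut into responders and non-responders, the tapering rate is Φ(Φ⁻¹(control rate) + 0.5). A control rate of 20% then gives 36.6% and power of about 55%. Over control rates from 5% to 50%, power runs from 32% to 59%.

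**The case against.** The strongest reply is that the design is coherent for its primary objective. Continuous MME, a comparison of means and sizing on Cohen's d belong together, the stated number reproduces, and the arms are compared at 4 months. All of that stands. A reader might infer that the stated hypothesis is never tested, but this goes too far: the superiority part is addressed. Naming a paired t-test for two independent arms is a separate defect and does not bear on this point.

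A reader might also infer that d = 0.5 was meant as a 50% reduction and that the sample size is therefore wrong. The article nowhere equates the two. Half an SD is 50% of the mean only if SD equals the mean, and the size is right for what it sizes.

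A third tempting inference is that 140 participants are ample for a responder comparison. This holds for some assumed rates and fails for others, so the document does not support it.

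It is also fair to say that means with 95% confidence intervals will be reported, so readers would see the size of the reduction, and that nothing announces an intention to present a significant p-value as proof of 50%. At a CV of 1.5, significance itself already needs a difference above 50%. These replies limit the harm. They do not say what evidence would support the 50% part.

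Finally, an analysis plan that is not shown might contain a responder analysis. That would fill the analytic gap. It would not correct a sample-size section that opens with a definition it does not use.

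**Conclusion.** The point holds in this limited form: the at-least-50% part of the hypothesis and the responder definition are tied to neither the sample size nor any analysis in the article. Only superiority on MME at 4 months is sized and tested, so a significant MME difference would not show a reduction of at least 50%.

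That conclusion rests on the text and on the exact reproduction of 70 per group, not on assumptions. Its practical size does rest on assumptions. The smallest significant difference lies between 25% and 53% of mean MME for CVs of 0.7 to 1.5. Responder power at 63 per arm lies between 63% and 95% in the four tabulated cases, and lower if the effect is only a 0.5 SD shift. The number of participants need not change. The matter is more than wording, because the plan as written leaves part of its own question without an answer.

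**What to change.** 1. Add as a secondary outcome the between-arm difference in the proportion with at least a 50% reduction in register MME from baseline to 4 months, with a 95% CI.

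2. Use a comparable look-back window at both time points for this outcome. The present 90 days at baseline and 30 days at 4 months could misclassify a participant whose dispensing falls outside the shorter window. The windows should also match between arms: as worded, the controls' value at their second baseline visit may fall under the 90-day rule.

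3. State that the 50% claim rests on a confidence interval for the tapering arm's reduction from baseline, for example that its lower 95% limit is at or above 50%, and not on the superiority p-value. Name the summary in advance (reduction in mean MME, or mean of individual percent reductions), since the latter is sensitive to participants with low baseline doses. Otherwise, remove the 50% part from the hypothesis.

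4. Say in Sample size {14} that 70 per group rests on a difference in mean MME and not on the responder definition. Add that power for the responder comparison depends on rates not yet given, with the range shown above.

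The cost is one more secondary analysis, some rewording and a stricter bar for the 50% claim. No patients or new data collection are needed: register MME is retrieved even for participants who discontinue (Plans to promote participant retention {18b}). Register data are drawn only when all follow-ups are closed ({18a}), so this can be settled before then.

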### Trial design {8}

The design of the present study is an RCT, which is under recruitment and conducted among patients with long-term pain who have been accepted to undergo a structured intervention aiming to taper opioid long-term treatments. The study population will be randomly allocated to either (1) the start of tapering opioids immediately or (2) the control group who will return to usual care and commence tapering of opioids 4 months later. A 12-month follow-up after the start of the intervention is included (Fig. 1). The study lies within a superiority framework. Primary endpoints are hypothesized to generate a decrease in opioid use in comparison to controls.

**Fig. 1 Fig1:**
[figure not shown]
Flow-chart TOPIO from baseline to follow-up

## Methods: participants, interventions, and outcomes

### Study setting {9}

Participants will be recruited from a population referred to tertiary pain clinics at three sites in Sweden: (1) Pain Rehabilitation Clinic of Skane University Hospital in Lund, (2) Pain Centre Sahlgrenska University Hospital in Gothenburg, and (3) Pain and Rehabilitation Centre in Linköping.

### Eligibility criteria {10}

Inclusion criteria are age ≥ 18 years with long-term (> 3 months) non-malignant pain and long-term prescribed opioid consumption (> 3 months) with a participant and/or prescribing doctor calling for tapering of opioids. All pain classes will be included, i.e., nociceptive pain (both somatic (musculoskeletal) and visceral), neuropathic pain, and nociplastic pain. Tapering of opioids is thus proposed without regard to pain mechanism or diagnoses. The requirement regarding functioning is (1) that a participant is able to absorb and retain information and is thus able to make an informed decision and (2) is at a functional level that permits outpatient visits.

Exclusion criteria at baseline are repeated intake of non-prescribed opioids or other illegal drugs, refusal to perform drug screening, prescription periods shorter than 3 months, and perceived medical risks of waiting with tapering of opioids (e.g., raising opioid doses after acute pancreatitis caused by excessive alcohol intake or kidney disease stage 4–5 in combination with excessive alcohol intake and high doses of opioids). The occurrence of substance use disorder without the use of illicit drugs is not an exclusion criterion.

Exclusion criteria were selected as a safety option to the physician at baseline visit when estimating the individual risks of the ongoing opioid treatment with regard to both overdose and development of dependence whenever a short duration (< 3 months) of treatment has occurred.

Otherwise, eligible participants who chose to not be included in the Swedish Quality Registry for Pain Rehabilitation (SQRP) will also be excluded.

The intervention will be carried out by physicians and nurses employed at tertiary pain clinics.

